#### Home-based self-monitored pulmonary rehabilitation program

##### Exercise training

Participants will undertake an aerobic and strength training program of similar intensity and duration to the hospital program. The initial walking speed will be set at 80% of the speed walked during a 6-minute walk test (6MWT). A goal for walking distance will be set and distance will be recorded using a pedometer
[31]. Participants will be encouraged to exercise for 30 minutes, five times per week and to record the completion of this activity in a home diary. Resistance training for the arms and legs will utilise daily activities and equipment that is readily available in the home environment (e.g. step-ups on an internal or external step, sit to stand from a standard height chair, water bottles for upper limb weights). To ensure safety and understanding of this exercise program, the initial exercise prescription will be established during a home visit by a physiotherapist. During this visit, elements of the self-management program that cannot be adequately discussed by subsequent telephone follow up will also be reviewed, including review of inhaler technique.

Participants will then be contacted by a physiotherapist each week by telephone for seven weeks to review the home diary, progress the exercise prescription and deliver self-management training. Disease specific self management training and exercise progression will be achieved using the principles of motivational interviewing
[32,33]. The aims of this training are to advance disease knowledge, promote problem solving and facilitate health behaviour change
[34]. Structured telephone modules will be used, with written prompts for the interviewer to explore and build motivation for change, then move towards commitment and action
[32]. Exercise goals will be discussed and documented each week in the home diary. Participants will also be provided with a menu of topics covering other aspects of self management that are routinely discussed in a pulmonary rehabilitation program
[29], including recognition and treatment of acute exacerbations; medication use; home exercise and physical activity; managing breathlessness; good nutrition; smoking cessation; and accessing community supports. Participants will be encouraged to choose one topic that is relevant to them for discussion and goal setting each week. Health goals will be documented in the standardized home diary. Training in self-management of acute exacerbations is considered a key element of pulmonary rehabilitation
[29] and this topic will be discussed at least once during the program. Consistent with the principles of motivational interviewing, collaborative discussions will be directed toward building the perceived importance of behaviour change, increasing confidence, identifying motivations for change and setting specific goals though emphasis on participants producing their own arguments for change
[32]. The physiotherapists undertaking the intervention will complete formal training in motivational interviewing and receive followup support from an experienced motivational interviewing practitioner.

At the completion of the 8-week intervention period, participants of both groups will be encouraged to continue with their home exercise program according to the previously outlined frequency and will be instructed to document their exercise participation in a monthly diary. Usual practice at both trial sites is to offer participants the opportunity to be involved in a community-based maintenance pulmonary rehabilitation program, in line with national standards
[27]. Participants in both groups will be offered this option and the proportion of participants that accept and attend will be documented.

### Outcome measures

Baseline demographics of age, gender, body mass index and lung function (spirometry) will be collected. Spirometry will be repeated at 12 months to determine stability of lung function. Completion rates will be collated at the end of the intervention period and compared between the hospital and home-based groups, with an *a priori* definition of completion as undertaking a minimum of 70% of planned pulmonary rehabilitation sessions
[35].

Clinical measures will be recorded at baseline, immediately following the intervention period (9 weeks) and at 12 months post completion of the intervention. An independent assessor, blinded to group allocation, will undertake the following measurements at each time point following the intervention period.

1) Functional exercise capacity will be measured using the 6-minute walk distance (6MWD), which is a valid measure of exercise capacity in COPD and is responsive to pulmonary rehabilitation
[36]. Two tests will be conducted on each testing occasion using a standardised protocol
[36], with the greatest distance recorded.

2) Dyspnoea will be measured using the Modified Medical Research Council Scale
[37].

3) Disease-specific HRQOL will be measured using the self-reported Chronic Respiratory Disease Questionnaire (CRDQ), a valid and responsive tool in pulmonary rehabilitation
[38]. It is comprised of 20 questions and assesses the domains of dyspnoea, fatigue, emotional function and mastery according to a 7-point Likert scale, with a higher score indicating better HRQOL.

4) A preference-based measure of HRQOL will be derived from the Short-form 36 (SF-36), a generic quality of life measure which is validated in COPD
[39]. Responses to SF-36 will be used to classify health states using the SF-6D, for economic analyses
[40].

5) Self efficacy will be measured using the Pulmonary Rehabilitation Adapted Index of Self-efficacy (PRAISE), a tool derived from the General Self-efficacy scale
[41]. It is composed of 15 statements, each of which is scored from 1 to 4, with a higher score indicating greater levels of self efficacy. It is reproducible and sensitive to change following pulmonary rehabilitation in individuals with COPD
[41].

6) Anxiety and depression will be measured with the Hospital Anxiety and Depression Scale (HADS). This questionnaire is designed to detect and measure the severity of anxiety and depression
[42]. It consists of a series of 14 statements, with responses based on a 4-point Likert scale. The HADS is self-administered and has demonstrated responsiveness to pulmonary rehabilitation
[43]. A higher score is indicative of greater anxiety or depression.

7) In a subgroup of participants, physical activity will be measured objectively using the SenseWear MF Armband (SWA, Bodymedia, Pittsburgh, USA) for a period of seven days. The SWA is a tri-axial accelerometer worn on the back of the left upper arm. The SWA produces estimates of energy expenditure and physical activity intensity using a proprietary algorithm (version 7.0), as well as measured outputs (step count). This monitor has been validated for assessment of daily activity
[44] and used to monitor physical activity participation
[45,46] in people with COPD. Variables to be reported are total wear time, number of steps per day, total energy expenditure per day, metabolic equivalents (METs) per day, awake sedentary time and time spent in moderate and vigorous activities.

### Economic evaluation

Economic evaluation will include direct (health system) and indirect (personal) health care costs related to the interventions and the 12 month follow up period. Direct costs will include staff time, consumables, communications, overheads and staff transportation. Information on the costs of the intervention will be based on detailed information on staff inputs by duration, type and resource use. Personal costs to individuals will include transportation, travel time, and impact of the intervention on the economic activities of other household members. Health system costs will include the costs of the intervention(s) and the costs associated with the use of health services, such as visits to the general practitioner, specialist visits, emergency department visits and hospitalization in the 12 month follow up period.

Participants will be contacted by telephone every month during the year-long followup period to document self-reported health care utilization and to encourage completion of the monthly diary. Out of pocket medical expenses will be recorded. Hospitalisation data and use of hospital services will be confirmed by medical record audit at the end of the trial. Medical and pharmaceutical resource use will be confirmed directly via Pharmaceutical Benefits Scheme (PBS) and Medicare Benefits Schedule (MBS) data. Medical services, government-subsidised pharmaceuticals and hospitalisation will be valued according to costs derived from the MBS, PBS and the Australian Refined Diagnosis Related Groups. Costs under the two interventions will be compared to assess the incremental impact of home-based rehabilitation for health system and personal costs. Sensitivity analyses will be carried out using different assumptions about the cost of travel and other personal healthcare costs in people with COPD.

To determine an individual’s self-valuation or utility of health state at a specific point in time, the SF-36 will be used to classify health states using the SF-6D
[40]. This reflects six dimensions of health state including physical functioning, role limitations, social functioning, pain, mental health and vitality. Each attribute contains four to six levels that account for the 18,000 unique health states captured by the SF-6D. These indices are combined to provide a single preference utility index. Responses will be weighted by predetermined values established from the general population
[47], with the highest score being 1.0 (best health state) and the lowest score being 0.0 (worst health state)
[40] using the standard gamble utility measurement. This score will be converted to QALYs, which have the ability to simultaneously capture information about the gains achieved from reduced morbidity (quality gains) and reduced mortality (quantity gains)
[23] and have the assumption that the duration of each status is exactly one half of the time between two measurement intervals. An incremental cost-effective ratio will compare the differences in costs with differences in gains in QALYs between the two interventions.

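### Health-service use is costed only for the 12 months after the programme, so care during the 8–9 week intervention falls outside the stated cost scope and no common horizon with the QALYs is fixed

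*Protocol article*

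**What the plan says.** All cost statements are in the Economic evaluation section of the protocol article.

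- **Overall scope.** Direct and indirect "health care costs related to the interventions and the 12 month follow up period". The intervention and the follow-up year are named as two separate items.
- **Programme costs.** "Information on the costs of the intervention will be based on detailed information on staff inputs by duration, type and resource use". The direct-cost list is staff time, consumables, communications, overheads and staff transport.
- **Health-service use.** General practitioner and specialist visits are costed together with "emergency department visits and hospitalization in the 12 month follow up period".
- **Collection.** "Participants will be contacted by telephone every month during the year-long followup period to document self-reported health care utilization".
- **Checks.** "Hospitalisation data and use of hospital services will be confirmed by medical record audit at the end of the trial", and "Medical and pharmaceutical resource use will be confirmed directly via Pharmaceutical Benefits Scheme (PBS) and Medicare Benefits Schedule (MBS) data". Neither sentence gives a date range.

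The timing of the follow-up year comes from the Outcome measures section: "Clinical measures will be recorded at baseline, immediately following the intervention period (9 weeks) and at 12 months post completion of the intervention". The SF-36, from which the SF-6D is derived, is one of these measures. The Economic evaluation section then converts SF-6D scores to QALYs by giving each health state half of the interval between assessments, and forms an incremental ratio of costs to QALY gains. It does not say when the QALY horizon starts.

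**The concern.** The cost side is uneven within itself. In the programme weeks the cost of delivering each programme is counted, but an admission, emergency visit or general practitioner visit in the same weeks is not part of the stated definition and is not asked about in any planned call. This holds whatever start is chosen for the QALYs.

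Three features of this trial make those weeks important:

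- **Contrast between arms.** The hospital arm has supervised sessions twice a week with pulse oximetry. The home arm has one visit and seven weekly calls. After the programme, both arms receive the same advice and the same offer of maintenance. An effect of lower supervision on service use would be expected to show first in the programme weeks.
- **Cost category.** The Background says that hospital use accounts for most of the health-system cost of COPD and that rehabilitation is associated with fewer exacerbations and admissions. The uncosted item belongs to the dominant category, and the intervention may affect it.
- **No check that would reveal it.** The planned sensitivity analyses vary travel and other personal health care costs, so they would not expose the gap.

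At stake is the third aim, the cost comparison, and the hypothesis that the home programme is more cost-effective.

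**Working it through.** There is no stated figure to reproduce: the article gives no length for the economic horizon. The check compares time windows and then sizes the gap.

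**1. Windows side by side (Economic evaluation and Outcome measures)**

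| Item | Programme weeks | 12 months after completion |
|---|---|---|
| Programme delivery cost | Yes | Not applicable |
| General practitioner, specialist, emergency and hospital use | Not in the stated definition | Yes |
| Monthly utilisation calls | No | Yes |
| Record audit, MBS/PBS data | No start date given | No start date given; confirm use |
| SF-36/SF-6D | Baseline and 9 weeks | 12 months after completion |

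**2. Share of the horizon without service-use costs, if QALYs start at baseline**

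Inputs: the programme lasts 8 weeks (Interventions), the post-programme assessment is at 9 weeks (Outcome measures), and follow-up is 12 months, taken as 52 weeks. With w the uncovered weeks, share = w / (w + 52).

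- w = 9: 9 / 61 = 14.8%
- w = 8: 8 / 60 = 13.3%

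If QALYs were instead counted only from the 9-week assessment, the mismatch between the QALY window and the service-use window would be 0%.

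**3. Weights under the half-interval rule, same condition**

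In years, the assessments fall at 0, 9/52 = 0.173 and 0.173 + 1 = 1.173.

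- Baseline score: 0.173 / 2 = 0.087
- 9-week score: 1.173 / 2 = 0.587
- Final score: 1 / 2 = 0.500
- Total: 1.173 years (the rounded weights add to 1.174)

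The first interval supplies 0.173 of the 1.173 years, again 14.8%.

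**4. How the gap enters the incremental cost**

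Full cost difference = (costs the article counts) + (difference between arms in service-use cost during the programme). The second term is omitted. It is zero if in-programme use is equal in the two arms, and it can have either sign otherwise.

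**5. How many events could be involved**

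The article gives no admission rate, so the rate is an assumption: 0.2 to 1.0 admissions per patient-year. With 166 randomised, each arm has 166 / 2 = 83.

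- At 0.2: 0.2 × 9/52 = 0.035 per patient; × 83 = 2.9 per arm
- At 0.5: 0.5 × 9/52 = 0.087 per patient; × 83 = 7.2 per arm
- At 1.0: 1.0 × 9/52 = 0.173 per patient; × 83 = 14.4 per arm

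These are events falling in the uncosted weeks, not a bias. The bias depends on how they differ between arms and on unit costs, which the article does not give.

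**The case against.** The case on the other side has four parts.

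- **The sources may cover the programme weeks.** The opening scope sentence is broad, and the audit, the MBS/PBS data and the out-of-pocket record have no stated start date. This stands in part: a reader might infer that the programme weeks are certainly excluded and lost, and the text does not support that. Admissions and subsidised services in those weeks would still be on record when the audit is done at trial end. But these sources are described as confirming use, no self-reported use is collected for the programme weeks, and the cost definition itself names the follow-up year.
- **The QALY start is not stated.** This stands. Three SF-36 assessments and the half-interval rule point to baseline, but the baseline score could serve only as a reference value. The 14.8% is therefore conditional.
- **The utility side may also miss these events.** This stands. No SF-6D score is taken between baseline and 9 weeks, so an exacerbation that resolves before the 9-week assessment need not change either score. It cannot be said that in-programme events always lower QALYs without entering costs. The Background also reports that earlier home programmes were found to be safe.
- **A journal article leaves economic detail to fuller documents.** This holds for extraction dates and similar detail, and an omission of that kind would not be raised. It does not answer the main point, because the article does state a window for service-use costs, and that window starts after the programme.

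**Conclusion.** The point holds as a gap in the stated cost scope. Followed as written, the plan costs programme delivery in the first 8–9 weeks but not health-service use in the same weeks, and it fixes no common horizon for costs and QALYs. If QALYs run from baseline, 14.8% of the horizon (13.3% using 8 weeks) has QALYs without service-use costs. The incremental cost could be biased if in-programme use differs between arms. Neither the direction nor the size can be derived from the article.

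A reader might go further and infer that a few admissions would reverse the cost result. The article gives no unit costs, admission rates or programme costs, so that is not shown. The change is worth making because it concerns a stated aim and costs little. It bears on the economic analysis only and does not affect the primary outcome, the change in 6-minute walk distance.

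**What to change.** 1. State one horizon for costs and QALYs: randomisation to 12 months after programme completion. Reword the health-service cost definition to match.
2. Start the planned record audit and the MBS/PBS extracts at the randomisation date.
3. At the 9-week visit, ask the existing utilisation and out-of-pocket questions once, covering the programme period.
4. State that QALYs are counted from baseline over the same horizon.

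The cost is a changed start date in data requests already planned and one short questionnaire at an existing visit, with a slight recall burden over about 9 weeks. The article reports that recruitment is continuing, so later participants can be asked prospectively. For those already past the 9-week visit, the audit and claims data can still supply hospital and subsidised medical use, while self-reported items and out-of-pocket expenses would be harder to reconstruct.

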There is a need for new models of pulmonary rehabilitation which allow all program components to be delivered at home, with proven clinical outcomes and low costs. The aims of this study are to 1) compare completion rates of a home-based self-monitored pulmonary rehabilitation program with a hospital-based, outpatient program in people with COPD; 2) compare the clinical benefits of home-based pulmonary rehabilitation and hospital-based pulmonary rehabilitation and 3) compare the costs of home-based and hospital-based pulmonary rehabilitation. We hypothesise that the proportion of patients who complete pulmonary rehabilitation will be greater in the home-based intervention; the clinical effects on exercise capacity, symptoms and quality of life will be equivalent in both models; and the home-based program will be more cost-effective.

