### Analysis

Continuous variables will be examined with repeated measures analysis of variance and linear mixed models, as appropriate. The proportion of participants who complete the program will be compared between groups using a chi-squared test and the relative risk of non-completion will be determined. All data will be analysed by intention to treat. A per-protocol analysis will also be conducted to reduce the risk of Type 1 error, as recommended in the CONSORT Extension for reporting of non-inferiority and equivalence trials
[48]. Alpha will be set at 0.05.

Sample size calculations are based on the primary outcome of change in 6MWD. If there is truly no difference in the change in 6MWD between home-based and hospital based groups, then 144 participants are required to be 80% sure that the 95% confidence interval will exclude a difference in means of more than 25 metres. We have recently demonstrated that this is the minimal important difference for 6MWD in our population of patients with COPD
[49]. This assumes a standard deviation of the change in 6MWD of 51 metres
[50]. On the basis of our previous trials in pulmonary rehabilitation
[49,50], we expect 15% attrition from the study; we will therefore randomize a total of 166 participants.

This sample size will also provide appropriate power for the secondary outcomes:

***Completion:*** Data from our centres indicate that only 66% people who are referred to pulmonary rehabilitation take up the referral and complete the centre-based program. Previous studies have documented very high completion rates for home-based programs of over 90%
[18]. Using a more conservative estimate of 85% completion, 144 patients will be required to detect a difference in completion rates between hospital and home-based groups (72 in each group).

***Dyspnoea:*** If there is truly no difference in the change in the dyspnoea domain of the CRQ between home-based and hospital based groups, then 142 participants are required to be 80% sure that the 95% confidence interval will exclude a difference in means of more than 2.5 points. This is the minimal important difference for the dyspnoea domain of the CRQ
[51] and assumes a standard deviation of the change in CRQ dyspnoea of 5.1 points
[50].

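### The only named cost-effectiveness statistic is a ratio whose denominator the trial expects to be near zero, so it cannot by itself support the hypothesis that home rehabilitation is more cost-effective

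*Protocol article*

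**What the plan says.** The hypotheses at the end of the Background are that "the clinical effects on exercise capacity, symptoms and quality of life will be equivalent in both models" and that "the home-based program will be more cost-effective". Under Outcome measures, the utility is taken from a quality-of-life questionnaire: "Responses to SF-36 will be used to classify health states using the SF-6D, for economic analyses". Economic evaluation converts that utility to QALYs and closes with the summary statistic: "An incremental cost-effective ratio will compare the differences in costs with differences in gains in QALYs between the two interventions". The article names no other cost-effectiveness statistic.

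Two further statements in the same section bear on the point. Costs are also to be compared on their own: "Costs under the two interventions will be compared to assess the incremental impact of home-based rehabilitation for health system and personal costs". The sensitivity analyses that are named concern the cost side: "Sensitivity analyses will be carried out using different assumptions about the cost of travel and other personal healthcare costs in people with COPD".

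**The concern.** The SF-6D is a quality-of-life measure, so the equivalence hypothesis covers the source of the QALYs. If that hypothesis is right, the trial divides a cost difference by a quantity centred close to zero. Such a ratio is badly behaved in two ways.

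- **Sign.** Suppose home rehabilitation saves money. A trivially positive QALY difference then gives a negative ratio (home dominates), and a trivially negative one gives a positive ratio (home is cheaper but slightly worse). A negative ratio also arises when home is dearer and worse. Its sign alone does not say which programme is preferable.
- **Size.** The closer the estimated QALY difference is to zero, the larger the ratio becomes, without limit. Its magnitude mainly reflects how close to zero the denominator happened to fall.

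At stake is the third hypothesis, that home is more cost-effective. The difficulty is greatest in the scenario the trial is designed to demonstrate. The named sensitivity analyses change only the numerator and leave it in place.

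**Working it through.** The article states no QALY difference, QALY SD, cost difference or value of the ratio, so there is no figure to reproduce.

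**Inputs from the article.** There are 144 evaluable participants (Analysis: "144 participants are required to be 80% sure that the 95% confidence interval will exclude a difference in means"), or 72 per arm. Applying the 15% attrition to the 166 randomised gives 166 × 0.85 = 141, or about 70 per arm.

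**Assumed inputs, not in the article.** QALY SD 0.05 to 0.20; true QALY difference 0 to 0.03; three pairs of cost saving and cost SD (table below); 50,000 per QALY as the willingness-to-pay value. Write dQ and dC for home minus hospital in QALYs and costs.

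**Step 1: the denominator.** SE(dQ) = SD × √(2/n), and P(estimated dQ < 0) = Φ(−dQ/SE). With a true dQ of 0 this is Φ(0) = 0.50, and the 95% CI for dQ includes zero in 95% of trials. Neither figure depends on the SD or the sample size.

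**Step 2: a small true difference does not cure it.** With 72 per arm, √(2/72) = 0.1667. The last column is 2.8 × SE.

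| QALY SD | SE(dQ) | Wrong sign if true dQ = 0.01 | 95% CI for dQ includes 0 if true dQ = 0.01 | True dQ for 80% power against 0 |
|---|---|---|---|---|
| 0.05 | 0.0083 | 11.5% | 78% | 0.023 |
| 0.10 | 0.0167 | 27% | 91% | 0.047 |
| 0.15 | 0.0250 | 35% | 93% | 0.070 |
| 0.20 | 0.0333 | 38% | 94% | 0.093 |

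**Step 3: the ratio and net benefit when the true dQ is 0 and the QALY SD is 0.10.** Net monetary benefit is NMB = 50,000 × dQ − dC, with SE = √[(50,000 × SE(dQ))² + SE(dC)²]. The ratio ranges are from simulation with normal draws.

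| Per arm | Saving | Cost SD | Central 95% of dC/dQ | NMB mean | NMB 95% range | P(NMB > 0) |
|---|---|---|---|---|---|---|
| 72 | 300 | 500 | about ±0.29 million | 300 | about −1,340 to 1,940 | 0.64 |
| 72 | 500 | 5,000 | about ±0.75 million | 500 | about −1,810 to 2,810 | 0.66 |
| 70 | 500 | 8,000 | about ±1.1 million | 500 | about −2,600 to 3,600 | 0.62 |

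*Hand check of the first row.* A standard normal lies within ±0.0627 of zero with probability 0.05. So |dQ| falls below 0.0627 × 0.0167 = 0.00105 in 5% of trials, and 300/0.00105 is about 0.29 million. For NMB, 50,000 × 0.01667 = 833 and SE(dC) = 500 × 0.1667 = 83. The SE is √(833² + 83²) = 838, and 300 ± 1.96 × 838 gives about −1,340 to 1,940.

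*Hand check of the last row.* √(2/70) = 0.1690, so SE(dQ) = 0.0169 and SE(dC) = 1,352. The NMB SE is √(845² + 1,352²) = 1,595, and 500 ± 1.96 × 1,595 gives about −2,600 to 3,600.

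**Step 4: sensitivity to the QALY SD.** In the last row, moving the SD from 0.08 to 0.12 changes the range from about ±1.36 million to ±0.91 million. In the first row, moving it from 0.05 to 0.15 changes the range from about ±0.57 million to ±0.19 million. In every first- and second-row scenario (QALY SD 0.05 to 0.15) about half of the simulated ratios are positive.

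**The case against.** The case on the other side has real weight.

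- **Costs are compared separately.** A reader might infer that the third aim cannot be answered. The article does not support that. The aim is to compare costs, and Economic evaluation plans that comparison directly. What remains is the hypothesis about cost-effectiveness, for which the article states no rule for the case of equal QALYs.
- **No interval or test for the ratio is stated.** A reader might infer that the plan will report an invalid confidence interval. None is mentioned, so there is nothing of that kind to criticise.
- **The components resolve the sign.** Someone who sees both differences can tell dominance from its opposite. That is correct, and it argues for making the components and a joint summary the result. It does not stabilise the ratio's size, or its sign from one trial to the next.
- **Detail may sit in a fuller plan.** Bootstrap methods, a cost-effectiveness plane, an acceptability curve and willingness-to-pay values are commonly left out of an article, and their absence is not a finding. The point is the choice of statistic that the article does state.
- **Equivalence does not mean a zero QALY difference.** No QALY margin is set, QALYs also capture mortality, completion is expected to be higher at home, and the Discussion allows that benefits may last longer there. A true difference is therefore possible, but step 2 shows that small ones leave the ratio unstable.
- **Net benefit is imprecise too.** This stands. In step 3 its 95% range includes zero in every row.

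**Conclusion.** The concern holds in a limited form. The ratio is the only cost-effectiveness statistic named, and its denominator is expected to be near zero under the trial's own hypothesis. By itself it cannot support the claim that home rehabilitation is more cost-effective. That conclusion needs no outside figure, only the hypothesis of equal quality of life.

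The size does rest on assumptions. With a true QALY difference of 0, a QALY SD of 0.10 and about 70 per arm, the central 95% of ratios spans about ±0.29 million to about ±1.1 million per QALY. The nearly fourfold spread comes almost entirely from the assumed costs. If the true QALY difference were as large as about 0.023 (SD 0.05) to 0.093 (SD 0.20), the denominator would be separated from zero with 80% power and the problem would largely recede.

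The primary outcome and the comparison of costs are untouched. Nor does it follow that net benefit would settle the hypothesis: in the illustrations the probability that home is cost-effective is only 0.62 to 0.66. The gain is a result with a finite interval and a fixed direction. The change should be made before analysis, but it concerns a secondary, economic question.

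**What to change.** Change the closing statement of Economic evaluation so that:

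1. the main cost-effectiveness result is incremental net monetary benefit (willingness to pay × QALY difference − cost difference), with a bootstrap 95% CI, over a range of willingness-to-pay values named in advance;
2. the cost difference and the QALY difference are reported separately, with a cost-effectiveness plane or acceptability curve to show their joint uncertainty;
3. the incremental cost-effectiveness ratio is kept as a descriptive figure only.

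The cost is a change of wording and a little programming on data already to be collected, with no effect on trial conduct. The team must commit to a willingness-to-pay range, and should say openly that net benefit may remain imprecise with about 70 per arm.
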